### Statistical analysis

For patient characteristics, descriptive statistics will be used. The inclusion, exclusion and dropout numbers and reasons will be described. The results will be analyzed via intention-to-treat analysis and per-protocol analysis. The statistical framework for this trial is that of a superiority trial. For the primary endpoint, a generalized linear mixed model with a binomial distribution and logit link function will be used for the analysis at the individual level, adjusting for clustering. In the regression model, the treatment group (intervention/control) and the type of hospital (university/general) are used as a fixed effect and the cluster is used as a random effect. A correction with degrees of freedom is applied (between-within method) in connection with the type I error caused by the small number of clusters.

For DRAs over time (30 days, 3 months and 12 months) an unstructured residual covariance matrix will be included, and the time effect and interaction between time and interventions will be evaluated. A similar model will be applied to other binary outcomes. For these outcomes, the proportion of patients with events and the time to first event will be analyzed, similar to the primary outcome. For the analysis of the continuous secondary endpoints, a linear mixed model with the same random effects and correction method will be used. For all linear outcomes, mean differences with corresponding 95% confidence interval (CI) will be presented, and for binary outcomes, odds ratios with 95% CI will be reported. Mortality over time will be evaluated via multi-level survival analysis, and differences between groups will be presented as hazard ratios with 95% CIs. For ordered variables, multilevel mixed-effects ordered logistic models will be used. Statistical analyses will be performed via STATA 18 (StataCorp. 2023. *Stata Statistical Software: Release 18*. College Station, TX: StataCorp LLC), SPSS (IBM Corp. Released 2023. IBM SPSS Statistics for Windows, Version 29.0.2.0 Armonk, NY: IBM Corp) or RStudio (RStudio Team (2024). RStudio: Integrated Development for R. RStudio, PBC, Boston, MA URL http://www.rstudio.com/).

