### Sample size calculation

For the calculation of the sample size, we estimated that the proportion of patients with a DRA in the target group studied is approximately 20% [5]. Previous studies have indicated that multicomponent interventions with a focus on medication optimization can achieve a decrease in DRAs of 6%, i.e., a total readmission rate of 14% [20, 40, 41]. Using a sample size of 1,224 patients in both the intervention and control groups, which are divided into eight clusters of 153 patients in each group, a 6% decrease can be detected from the standard readmission rate of 20% (two-sided, power 80%, alpha 5%). An intracluster correlation coefficient (ICC) of 0.0065 was used, which is based on an estimated ICC between 0.005 and 0.01. With an ICC of 0.01, this group size would be sufficient to demonstrate a one-sided difference of 6% in favour of the intervention. A drop-out rate of 5% is expected [42], requiring a total of 161 patients per cluster to be included, or 2,576 in total. The sample size was calculated via PASS 2020 Power Analysis and Sample Size Software (NCSS, LLC. Kaysville, Utah, USA).

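### As written, the time-by-intervention test uses within-hospital degrees of freedom and has no term for hospital-specific change, so it is anti-conservative if hospitals change differently over follow-up

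*Protocol article*

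**What the plan says.** All of this is in the protocol article, Statistical analysis, except the sample-size inputs.

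- Primary model: a logistic mixed model in which treatment group and hospital type "are used as a fixed effect and the cluster is used as a random effect".
- Small-sample correction: "A correction with degrees of freedom is applied (between-within method) in connection with the type I error caused by the small number of clusters".
- Repeated DRA outcome: "For DRAs over time (30 days, 3 months and 12 months) an unstructured residual covariance matrix will be included", after which "the time effect and interaction between time and interventions will be evaluated".
- Other outcomes: the remaining binary outcomes get a similar model. For continuous secondary endpoints, "a linear mixed model with the same random effects and correction method will be used".
- Sample size calculation: eight clusters of 153 patients per arm, and "An intracluster correlation coefficient (ICC) of 0.0065 was used", chosen from a range of 0.005 to 0.01.

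No hospital-by-time random effect is named, and no figure is given for how much hospitals differ in their change over time.

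**The concern.** A single hospital effect is constant over time, so it drops out of any comparison of one visit with another inside the same hospital. The residual covariance matrix, read in the usual way, describes correlation between visits of the same patient. Neither represents hospitals whose outcomes move differently between 30 days, 3 months and 12 months.

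The between-within method does not fill the gap. It gives hospital-level degrees of freedom to effects that are constant within a hospital, such as treatment. Effects that vary within a hospital get within-hospital degrees of freedom, and time-by-treatment is one of them. Yet the interaction compares the time trends of eight hospitals with those of eight others. The correction is there to guard type I error with few clusters, and for this test it does not.

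At stake is a statement that the effect of the intervention fades or grows over the year, when chance differences in hospital drift could explain it.

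**Working it through.** **Reproducing the plan's own figure.** For 20% versus 14%, two-sided 5%, 80% power, individual randomisation needs 615 per arm. The design effect is 1 + (153 − 1) × 0.0065 = 1.988, and 615 × 1.988 ≈ 1,223, against the stated 1,224. The planned design and ICC are therefore understood correctly.

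**Degrees of freedom.** With complete data there are 2,448 × 3 = 7,344 records. Removing 16 hospitals, 2 time terms and 2 interaction terms leaves 7,344 − 16 − 4 = 7,324 within-hospital degrees of freedom. At hospital level there are 16 − 2 = 14, or 16 − 3 = 13 once hospital type enters. The critical values are 1.96 against 2.14 (14 df) or 2.16 (13 df).

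**Omitted variance, continuous outcome, single contrast.** Inputs: m = 153 and ICC = 0.0065 (Sample size calculation). Two quantities are assumed, because the article gives neither: c, the correlation of a hospital's effect between two times, and r, the within-patient correlation. True variance over model variance of the difference in change is

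D = 1 + m × ICC × (1 − c) / [(1 − ICC)(1 − r)],

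and the actual type I error is 2 × [1 − Φ(1.96/√D)]. With r = 0.5 the denominator is 0.9935 × 0.5 = 0.49675 and m × ICC = 0.9945.

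| c | D | √D | Type I error |
|---|---|---|---|
| 1 | 1 | 1 | 5.0% |
| 0.9 | 1 + 0.09945/0.49675 = 1.20 | 1.10 | 7.4% |
| 0.8 | 1 + 0.1989/0.49675 = 1.40 | 1.18 | 9.8% |
| 0.5 | 1 + 0.49725/0.49675 = 2.00 | 1.41 | 16.6% |

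Sensitivity at c = 0.9 and 0.8: ICC 0.005 gives 6.8% and 8.7%; ICC 0.01 gives 8.7% and 12.3%. Raising r to 0.75 at ICC 0.0065 gives 9.8% and 14.4%.

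**Fitting the linear model as described.** The fit was by REML, with a hospital intercept, unstructured residual covariance, 16 hospitals of 153, complete data, hospital type omitted, ICC 0.0065, r = 0.5 and 1,500 runs per setting. For c = 1, 0.9, 0.8 and 0.5:

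- The single 12-month-versus-30-day contrast rejected 5.5%, 8.6%, 9.3% and 16.9%.
- The 2-df interaction test rejected 6.0%, 8.5%, 12.2% and 21.9%.
- A t test on hospital-level mean changes with 14 df rejected 5.1% to 5.5% throughout.

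The unstructured residual matrix therefore does not absorb the missing variation.

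**Cumulative DRA.** This was a simulated 2-df test on the logit scale, using a complete-data approximation and not a fit of the planned mixed model. ICC was 0.0065, with assumed cumulative rates of 20%/25%/30% or 20%/27%/40%. The correlation here is between hospital effects in successive follow-up intervals.

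| Correlation | Type I error |
|---|---|
| 1 | about 5% |
| 0.9 | 5.7% to 7.0% |
| 0.8 | 6.2% to 7.2% |
| 0.5 | 8.0% to 10.5% |
| 0 | 11.4% to 15.7% |

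**Are both parts of the remedy needed?** If the hospital-by-time term is added but the within-hospital degrees of freedom are kept, a contrast with 13 true df is judged against 1.96 and rejects 7.2% of the time. So yes.

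**How often would the new variance be estimated at zero?** With balanced data and 14 df this is approximately the probability that a chi-square on 14 df falls below 14/D: about 37% at c = 0.9 and 24% at c = 0.8 (ICC 0.0065, r = 0.5).

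**The case against.** The strongest reply is that this reads too much into a condensed article. The words on the random effect describe the primary model. The sentence on DRA over time does not restate the random effects, the level of the residual matrix or the degrees of freedom for the interaction, and a fuller plan could add a hospital-by-time term. That is fair as far as it goes. But the article does state a random-effects structure and a correction method, and it carries both explicitly to the continuous outcomes. Adding the term would change what is written rather than fill in a detail.

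A reader might infer that the test will reject too often in this trial. The documents do not support that. Inflation requires hospitals to differ in their change over time, and nothing in the article says by how much. Such differences are plausible, since the article expects usual care to vary between hospitals and says that not all variability between hospitals can be avoided, but plausibility is not a figure.

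A reader might also apply the larger continuous-outcome figures to DRA. They do not carry over. Twelve-month cumulative status contains 30-day status, and the inflation is modest when hospital effects are highly correlated. The ICC was set for the readmission outcome, and the article gives none for quality of life or daily functioning. The REML check answers the complaint that the model was never fitted for continuous outcomes, but not for the logistic DRA model.

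Finally, the interaction carries no decision rule, and change in effect over time is not a listed endpoint. That stands and limits the severity.

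**Conclusion.** The point holds conditionally. Followed as written, the models test time-by-intervention on about 7,324 degrees of freedom where 13 or 14 are appropriate, with no term for hospital-specific change. Any such variation pushes type I error above 5%, and the stated correction gives no protection.

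The figures rest on the assumed correlations, on ICC 0.0065 and on complete data in 16 equal hospitals. A continuous single contrast comes to about 7% to 10% at hospital correlations of 0.8 to 0.9 and within-patient correlation 0.5. DRA comes to about 6% to 7% at the same hospital correlations and about 8% to 16% at 0.5 to 0.

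It would be wrong to extend this to the main result. The primary 30-day comparison has one time point, its treatment effect lies between hospitals, and between-within degrees of freedom suit it. Only a secondary analysis is affected: low to moderate severity, and a cheap improvement.

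**What to change.** In every model that tests time-by-intervention, add a random hospital-by-time effect and refer the interaction to hospital-level degrees of freedom: 14, or 13 if hospital type by time is also fitted. State in advance that if this variance is estimated at zero or the model does not converge, the interaction will be tested on hospital-level mean changes with the same degrees of freedom.

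The cost is two or three sentences in the analysis plan and one more variance term, with no new data. The interval for the interaction will be wider, and with 16 hospitals the fallback may be needed often (roughly a quarter to a third or more of trials in the settings above), so it should be written as a routine step.

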### Assessment of secondary outcomes

Secondary outcomes are assessed during index hospitalization and three follow-up telephone interviews at 30 days, and 3 and 12 months following discharge from the index hospitalization. The secondary endpoints include the proportion of patients with a DRA at 3 and 12 months after discharge, duration of DRA, time to first DRA, proportion of patients with a drug-related ED visit, proportion of patients with an all-cause readmission and ED visit, healthcare costs, QoL, cost-effectiveness, number of regular medications, ADL, proportion of patients living independently, proportion of patients with falls and mortality. For all binary outcomes listed above, outcomes are presented as both the proportion of patients experiencing at least one event and the total number of events per patient. In the intervention group, the number and type of recommendations in the pharmacotherapeutic plan and the number of implemented recommendations from the pharmacotherapeutic plan are collected as secondary outcomes.

If an admission or ED visit occurs, more detailed information about the ED visit and medication use is collected from the respective hospital to determine whether the ED visit was drug-related via the AT-HARM10 tool [38]. QoL, ADL and healthcare costs are assessed via the EQ-5D-5L, Katz-6 ADL and iMCQ questionnaires, respectively.

The data concerning medication use at admission and discharge is collected from the EHR during index hospitalization. Medication use during the follow-up period is assessed by asking patients or their representatives about the current medication use during follow-up telephone interviews. The number and types of recommendations in the pharmacotherapeutic plan are determined on the basis of the data collected at baseline about the execution of TMPC. The number of implemented pharmacotherapeutic recommendations is assessed by comparing the recommendations with the medication lists collected during follow-up.

If a patient is unable to answer questions concerning their current medication use during follow-up, the community pharmacy is contacted by the central research team to obtain a medication overview. If a patient cannot be reached, their survival status is identified by calling family members, the GP/elderly care physician or a member of the local research team from the participating hospital.

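### Time to first event is assigned the primary outcome's logistic mixed model, which uses neither event times nor censoring; survival methods are named for mortality only

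*Protocol article*

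**What the plan says.** All references are to the Methods of the protocol article.

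- **Assessment of secondary outcomes** lists among its endpoints the "proportion of patients with a DRA at 3 and 12 months after discharge, duration of DRA, time to first DRA". It adds that binary outcomes are presented both as the share of patients with one or more events and as event counts per patient.
- **Statistical analysis**, primary endpoint: "a generalized linear mixed model with a binomial distribution and logit link function will be used for the analysis at the individual level". Arm and hospital type are fixed effects, hospital is a random effect, and between-within degrees of freedom are used because there are few clusters.
- **Statistical analysis**, repeated status: "For DRAs over time (30 days, 3 months and 12 months) an unstructured residual covariance matrix will be included". A time effect and a time-by-arm interaction are then to be evaluated.
- **Statistical analysis**, other binary outcomes: a similar model applies, and for these outcomes "the proportion of patients with events and the time to first event will be analyzed, similar to the primary outcome".
- **Statistical analysis**, survival: "Mortality over time will be evaluated via multi-level survival analysis", with hazard ratios. No other outcome is given a survival method. Binary outcomes are to be reported as odds ratios.

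**The concern.** A time-to-event endpoint asks when the first event happened, among patients still under observation and still able to have it. A logistic model of event status asks only whether it happened by a fixed date. A DRA on day 20 and one on day 300 count the same in a 12-month analysis, and a patient lost to follow-up at month 4 must be dropped or classified by some other rule. If the sentence is followed as written, the timing information that justifies a separate time-to-first-event endpoint is discarded, and the result is an odds ratio that largely repeats the analysis of proportions.

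This is more than a detail left to the analysis plan, because the article assigns a method and the method does not suit the endpoint. Follow-up runs for a year in acutely admitted patients aged 70 or older, and only a life expectancy under three months is excluded. Some patients will therefore die without a DRA, so how death and censoring enter the analysis is not a side issue.

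The model for DRA status over time raises a related question: whether a residual covariance matrix and a test of the time effect make sense for a yes/no outcome that may be cumulative.

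**Working it through.** **1. The plan's own figure.** The point rests on no stated number. The sample size was reproduced to see whether it is touched.

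Inputs (Sample size calculation): 20% versus 14%, two-sided 5%, power 80%, ICC 0.0065, eight clusters of 153 per group.

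- Individually randomised, pooled-variance formula: [1.960·√(2·0.17·0.83) + 0.842·√(0.20·0.80 + 0.14·0.86)]² / 0.06² ≈ 614.1, so 615 per group.
- Design effect: 1 + (153 − 1)·0.0065 = 1.988.
- 615 · 1.988 = 1,222.6, against 1,224 stated. Power at 1,224 is 0.801.

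The figure reproduces. It concerns the primary proportion only, so nothing below changes it.

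**2. The passages side by side.**

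| Outcome | Method named | Uses event time or censoring? | Effect measure |
|---|---|---|---|
| DRA by 30 days (primary) | binomial-logit mixed model | no; not needed for a 30-day proportion | odds ratio |
| Other binary outcomes, proportion with events | similar model | no; not needed | odds ratio |
| Other binary outcomes, time to first event | as for the primary outcome | no; **needed** | none of its own |
| Time to first DRA (listed secondary) | none of its own; by analogy as above | no; **needed** | none of its own |
| Mortality | multilevel survival analysis | yes | hazard ratio |

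**3. The logistic effect is a different quantity.** Illustration with assumed constant hazards, none of them from the article: first DRA λ = 0.6 per year in controls, death μ = 0.25 per year in both arms, DRA hazard ratio 0.70 (so λ = 0.42 with the intervention). The probability of a DRA by time t is

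F(t) = λ/(λ + μ) · [1 − exp(−(λ + μ)t)].

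| Horizon | Control | Intervention | Odds ratio |
|---|---|---|---|
| 30 days | 0.0476 | 0.0336 | 0.695 |
| 3 months | 0.1351 | 0.0967 | 0.685 |
| 12 months | 0.4042 | 0.3061 | 0.650 |

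At 12 months: (0.3061/0.6939) / (0.4042/0.5958) = 0.650. The hazard ratio is 0.70 throughout, while the odds ratio moves with the horizon. The hazards are not calibrated to the plan: they give about 5% at 30 days, against the 20% used for planning. The table shows that the two measures differ, not by how much they will differ in this trial.

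**4. Residual covariance for DRA status.** The binomial variance is fixed by the mean, so a logit mixed model fitted by likelihood has no free residual covariance to estimate. A marginal or R-side model (GEE or pseudo-likelihood) can carry a working covariance, but the article does not say that one is meant.

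If status is cumulative, it can only move from 0 to 1. For s < t the correlation then follows from the margins:

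corr = (p_s − p_s·p_t) / √[p_s(1 − p_s)·p_t(1 − p_t)].

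For assumed proportions 0.20, 0.30 and 0.45:

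- 30 days with 3 months: 0.14 / √(0.16·0.21) = 0.76
- 30 days with 12 months: 0.11 / √(0.16·0.2475) = 0.55
- 3 with 12 months: 0.165 / √(0.21·0.2475) = 0.72

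Given the proportions, no correlation is left to estimate. The proportion cannot fall over time, so testing the time effect says nothing. The time-by-arm interaction stays interpretable.

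**The case against.** **The sentence may only list what is analysed.** It can be read as saying that both a proportion and a time to first event will be examined for the other binary outcomes, as for DRA, with the model for event times left to the analysis plan. Its direct subject is also the other binary outcomes, not time to first DRA. The reading is possible but strained. The primary outcome is a 30-day proportion with no time-to-event analysis of its own, so the comparison most naturally points to the model. On either reading, no survival method is named for any time to first event.

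**Cumulative status is inferred.** This stands. The definition by one or more events suggests it, but the Statistical analysis section does not say so. If status is interval-specific, the point about the time effect falls away.

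**A residual covariance is possible for binary data.** This stands for marginal or R-side models. The wording is ill-fitting, not impossible.

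**A reader might infer that deaths will bias the 3- and 12-month DRA proportions.** The article states no rule for deaths. With complete follow-up, counting DRA-free deaths as no DRA gives the cumulative incidence with death as a competing event, which is a legitimate quantity. It does respond to mortality. Under the assumed hazards above, with no effect on DRA, the 12-month odds ratio is 0.93 if the intervention arm's death hazard is 0.35 and 1.04 if it is 0.20. That is a reason to report a cause-specific hazard ratio beside it, not evidence of error in the proportion.

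**A reader might also infer an inflated type I error in the survival models.** With 16 hospitals and three hospital-level parameters there are 13 degrees of freedom, and P(|t₁₃| > 1.96) = 0.072. That applies only if normal critical values are used, and the article does not say they will be.

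**Drop-out is limited.** Expected drop-out is 5%. The general practitioner is contacted when a patient cannot be reached, hospital records are used and survival status is traced. Losses may therefore be few, but the model named still cannot use partial follow-up.

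**Conclusion.** The point holds in a limited form. The article gives time to first event a model that uses neither event times nor censoring, and keeps survival methods for mortality although time to first DRA is a listed endpoint. That is a badly fixed method for secondary endpoints. It rests on reading the comparison with the primary outcome as a statement about the model, which is the natural reading.

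The covariance wording is a lesser point. It is firm only for a likelihood fit, and the remark on the time effect holds only if status is cumulative.

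The size of any effect on results cannot be derived from the documents, since every hazard and later-horizon proportion used here is assumed. The documents support neither a claim that death distorts the DRA proportions by a given amount nor a claim of a 7% error rate. The 30-day primary analysis and the sample size are unaffected. The change should be made before the analysis starts.

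**What to change.** 1. Replace the time-to-first-event sentence with a named clustered time-to-event model for first DRA, readmission and ED visit. One choice is a cause-specific Cox model with a hospital frailty, in kind the approach already planned for mortality. Specify hospital type as a covariate, censoring at last contact, death as a competing event with cumulative incidence curves by arm, hazard ratios with 95% CIs, and a small-cluster correction in line with the primary analysis.
2. State whether DRA status at 3 and 12 months is cumulative or interval-specific. If cumulative, fit the primary model separately at each horizon and drop the residual covariance and the test of the time effect. The horizons will still share early events, so their odds ratios should be read as overlapping, not independent, results. If interval-specific, say so and name a marginal or R-side model for the covariance.
3. State how DRA-free deaths count in the proportions. Counting them as no DRA is acceptable if labelled as cumulative incidence.

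The cost is wording in the analysis plan and some programming, with no extra patients or visits. Confirm first that event and death dates are in the database: the article says that readmission details are requested from hospitals and that survival status is traced, which implies dates but does not state them.

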### Data collection

Baseline data collection is conducted by the local research team during index hospitalization. All local research personnel are trained in data collection through e-learning. At baseline, information is collected about demographics, independence of medication intake, use of medication aids, living situation, falls and fall-related injuries, laboratory results (e.g., electrolytes, renal function; collected in routine care), medical history, reasons for current admission and medication use at both admission and discharge. Furthermore, we collect data through various questionnaires, including EuroQol 5-dimensions 5-level (EQ-5D-5L) [33] for quality of life (QoL), the Katz-6 [34] for activities of daily living (ADL), the Clinical Frailty Scale [35] for frailty, and the iMTA medical consumption questionnaire (iMCQ) [36] for healthcare utilization and costs. In addition, data collection in intervention hospitals includes information about the recommendations given during the pharmacotherapeutic analysis, completeness of conducting TMPC elements and healthcare professionals involved, and duration of TMPC.

Outcome data are collected by a central research team during follow-up telephone calls with participants or their representatives at three time points: 30 days, 3 months and 12 months after discharge from the index hospitalization. Data concerning current living situation, falls and fall-related injuries, independence of medication intake, use of medication aids and current medication use are collected. Furthermore, the EQ-5D-5L, Katz-6 ADL and iMCQ questionnaires are repeated during each telephone interview. All central research employees are trained in performing the follow-up data collection. If a patient or representative cannot be reached after four attempts or if a patient does not wish to answer the questionnaires anymore but still wants to continue study participation, the patient’s GP or elderly care physician is contacted to ask only those questions required to answer the primary research objective.

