### Economic evaluation

An economic evaluation will be performed to investigate the cost-effectiveness of the intervention compared to usual care. Cost-effectiveness will be expressed in terms of the cost per quality adjusted life year (QALY) gained and via the net monetary benefit approach. Healthcare costs will be assessed via the iMCQ. Lost productivity costs will not be evaluated, as all participants are retired at an age of 70 years or older. Standard cost-prices per item of healthcare consumption will be determined via appendix 1 of the guideline for performing economic evaluations [43]. If standard prices are not available, the full cost prices of items will be used via activity-based costing. The costs of medication use will be derived from the Dutch formulary [44], increased with the cost for pharmacy care and will be based on the medication use confirmed during the follow-up telephone calls or the medication list from the community pharmacy. The costs of the intervention will be calculated through a time measurement of the intervention, which is based on the time spent by the pharmacotherapy-team members on the TMPC elements, and their average salary. For all participants, an overall time estimate will be made and in a selected group an exact time measurement per TMPC element will be executed. QoL will be measured by the EQ-5D-5L, which includes the Visual Analogue Scale. Furthermore, a budget impact analysis will be performed. The short- and midterm affordability of TMPC will be assessed from governmental, health care and insurer perspectives.

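### No baseline term is named for the continuous secondary outcomes or the QALY comparison, although baseline values are collected; adjustment should be written in

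*Protocol article*

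**What the plan says.** The Statistical analysis section describes the primary model term by term: "the treatment group (intervention/control) and the type of hospital (university/general) are used as a fixed effect and the cluster is used as a random effect", with a between-within correction for the small number of clusters. For continuous secondary outcomes it then states: "For the analysis of the continuous secondary endpoints, a linear mixed model with the same random effects and correction method will be used". Results are to be reported as mean differences with 95% confidence intervals. The section also provides ordered logistic mixed models for ordered variables, without saying which outcomes these cover. No baseline measurement is named in any of these models.

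The Data collection section lists EQ-5D-5L, Katz-6 and "the iMTA medical consumption questionnaire (iMCQ) [36] for healthcare utilization and costs" among the baseline instruments, together with "medical history, reasons for current admission and medication use at both admission and discharge". At follow-up, "the EQ-5D-5L, Katz-6 ADL and iMCQ questionnaires are repeated during each telephone interview", that is at 30 days, 3 months and 12 months. Assessment of secondary outcomes counts the index stay as one of the assessment points.

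The Economic evaluation section expresses results as cost per QALY and net monetary benefit and says that "QoL will be measured by the EQ-5D-5L, which includes the Visual Analogue Scale". It gives no estimation model and no covariates.

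**The concern.** For each of these measures, the patient's own baseline value is usually among the strongest predictors of the follow-up value. Leaving it out has two consequences.

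The first is precision: variation between patients that baseline could explain stays in the residual and widens the interval.

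The second is imbalance. Hospitals are allocated six months before recruitment starts (Randomization), local teams know their arm (Blinding), and patients consent after allocation (Participants). With eight hospitals per arm, baseline differences can arise by chance or through differential recruitment. The only covariate named, hospital type, does not deal with patient-level differences. An unadjusted comparison would read part of a baseline difference in utility as a treatment effect. The difference in QALYs is the denominator of the cost per QALY, so a small shift there can move that result considerably.

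**Working it through.** **The plan's own figure.** The article gives no precision or target difference for any continuous outcome. Its only size calculation is for the binary primary outcome, and that reproduces. For 20% against 14%, two-sided 5%, 80% power, 615 patients per arm are needed under individual randomization. The design effect is 1 + (153 − 1) × 0.0065 = 1.988, and 615 × 1.988 = 1,223, against 1,224 stated. Only the layout is used below: 8 hospitals per arm with 153 patients each.

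**Precision.** Inputs not in the article, hence assumed:
- ρ, the ICC of a continuous outcome, 0.005 to 0.05. The article's 0.005 to 0.01 refers to the primary outcome.
- r, the patient-level baseline to follow-up correlation, 0.3 to 0.7.
- r_c, the same correlation between hospital means.

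In SD units, the variance of the difference between arms is

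Var = 2 × [ρ(1 − r_c²) + (1 − ρ)(1 − r²)/153] / 8,

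and the unadjusted variance has r = r_c = 0.

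*Case 1, r_c = r.* The standard error (SE) ratio, adjusted to unadjusted, is √(1 − r²), whatever ρ is: 0.95 (r = 0.3), 0.87 (r = 0.5), 0.71 (r = 0.7). That is a reduction of about 5%, 13% and 29%.

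*Case 2, r_c = 0* (baseline explains no between-hospital variance). Example with ρ = 0.01, r = 0.5:
- Unadjusted: 2 × (0.01 + 0.99/153)/8 = 0.00412, SE 0.0642.
- Adjusted: 2 × (0.01 + 0.75 × 0.99/153)/8 = 0.00371, SE 0.0609.
- Ratio 0.95.

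| ρ | r = 0.3 | r = 0.5 | r = 0.7 |
|---|---|---|---|
| 0.005 | 0.974 | 0.927 | 0.850 |
| 0.01 | 0.982 | 0.950 | 0.899 |
| 0.02 | 0.989 | 0.969 | 0.939 |
| 0.05 | 0.995 | 0.986 | 0.973 |

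In this case the gain runs from 15% down to 0.5%. A hospital-level correlation above the patient-level one would instead give more than Case 1.

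**QALYs.** The article does not say how QALYs are computed. Assume the trapezoidal area under the utility curve at 0, 30/365, 0.25 and 1 year, and equal SDs at all visits, so that the regression slope equals r. The visit weights are:
- baseline: 0.0822/2 = 0.041
- 30 days: 0.25/2 = 0.125
- 3 months: (1 − 0.0822)/2 = 0.459
- 12 months: 0.75/2 = 0.375

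The three follow-up weights sum to 0.959. A baseline utility difference b leaves b at baseline and b × r at each follow-up visit, so the unadjusted QALY difference shifts by b × (0.041 + 0.959r).

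| b | r = 0.3 | r = 0.5 | r = 0.7 |
|---|---|---|---|
| 0.01 | 0.003 | 0.005 | 0.007 |
| 0.03 | 0.010 | 0.016 | 0.021 |
| 0.05 | 0.016 | 0.026 | 0.036 |

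**The case against.** The strongest reply is that this is a condensed article. The covariates of secondary models and the regression used for QALYs are commonly set out in the full protocol or analysis plan, neither of which is shown. The sentence on continuous endpoints carries over only the random effects and the correction method. It lists no fixed effects at all, so it is shorthand rather than a complete model.

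Much of this stands. A reader might infer that the trial will analyse these outcomes without their baseline values, or that the QALY result will carry recruitment imbalance. The documents support neither: the first reads silence as exclusion, and the second presumes a QALY model that is not described. It is also open whether Katz-6 belongs to the linear or the ordered logistic model, and costs are described under the economic evaluation rather than assigned to the linear model.

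A second reply is that the index stay is listed as an assessment point, so baseline could enter as a repeated outcome. That does not settle the matter. If each arm keeps its own baseline mean, the contrast at a follow-up visit is still essentially the unadjusted difference. Adjustment needs baseline as a covariate, a common baseline mean or a contrast of changes, and none is stated. The covariance structure and time interaction that the section does specify are for DRAs over time.

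A third reply is that the benefit may be very small. That is correct where between-hospital variance dominates and baseline does not explain it.

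**Conclusion.** The point holds as a matter of specification. Where the article names model terms, it names no baseline value for the continuous secondary outcomes, and it names no baseline-utility adjustment for QALYs or net benefit. Followed with only the stated terms, the analysis would be less precise than the collected data allow and open to measured baseline imbalance.

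How much less precise cannot be read from the article. Under the assumptions shown, the loss ranges from negligible to just under a third of the standard error, and the QALY shift from 0.003 to 0.036. The article gives no EQ-5D standard deviation, ICC or target difference, so these shifts cannot be compared with an effect the trial expects to detect. Adjustment removes only imbalance in what was measured; it does not cure recruitment bias in general.

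**What to change.** State in the analysis plan, before the cleaned dataset is released for analysis:

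- Each model for a continuous secondary outcome includes the pre-intervention value of the same measure as a fixed covariate, alongside arm and hospital type: EQ-5D index and VAS, and number of regular medications. A longitudinal model with a common baseline mean for both arms is an acceptable alternative.
- Katz-6 is adjusted for its baseline value in whichever model is used, linear or ordered logistic, and the plan says which.
- The medication baseline is the count at admission. The discharge list can already reflect TMPC, which is delivered during the same stay.
- Cost comparisons adjust for the baseline iMCQ cost.
- The QALY and net-benefit comparisons adjust for baseline utility.

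If the analysis plan already says this, confirming it is enough. The cost is wording only: the data are collected, and no visit, patient or procedure is added.
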